**Methods:**

The study is a single-center randomized controlled trial (RCT) with two study arms - intensive diabetes mellitus care versus routine clinical care. Patients in the intensive arm will receive care from a multidisciplinary team consisting of an endocrinologist, diabetes nurse educator, dietitian, renal pharmacist and medical social worker for counselling. In addition, patients will be provided with tools for self-care empowerment such as glucometers, blood pressure monitors and android tablets to facilitate care, monitoring and education. Patients in the routine clinical care arm will receive standard clinical care. Follow up (FU) will be for 3 years. Primary outcomes include cardiovascular events, rate of progression of nephropathy and development of end-stage renal disease. Secondary endpoints include the proportions of patients with documented improved control of cardiovascular risk factors (HbA1c, blood pressure, low density lipoprotein-C (LDL-C), reduction in body weight), frequency of hypoglycemia, hospitalization days and changes in femoral IMT. We will also examine the prevalence of peripheral atherosclerosis and the predictive value and usability of lower extremity arterial ultrasound to predict cardio-cerebrovascular events, amputation and peripheral intervention.

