### Eligibility criteria

Patients will be considered eligible for the study if they fulfil the following criteria:
Aged 21–70 yearsPoorly controlled T2DM as defined by HbA1c ≥ 9%Nephropathy as defined by estimated GFR (eGFR) 30–60 ml/min and/or proteinuria classified as urine protein > 0.5 g/day and/or urine albumin:creatinine ratio (ACR) >30 mg/mmol on two consecutive measurements 3 months apart

Patients will be excluded from study participation if any of the following criteria are present:
Type 1 diabetes mellitus defined as a history of ketosis at diagnosis (acute symptoms with heavy ketonuria (urine value > 3+) or ketoacidosis) or continuous requirement of insulin within 1 year of diagnosis.Psychiatric conditions being treated by medications that adversely affect patients’ weight and stability of their mental health.Patients on weight loss medications or have had bariatric surgery, which may affect their mental health and compliance with dietary advice.Life expectancy < 12 months due to advanced cancer or other life-threatening conditions, such that they will not be able to perform self-care or complete 3 years of follow-up.Pregnant or lactating patients.

Patients will be withdrawn from the study if any of the following criteria apply:
The patient withdraws consentThe patient is no longer able to participate or the investigator, in discussion with the patient’s attending physician(s), decides to terminate participation on medical groundsThe patient becomes pregnant during the study

There will be no participant replacement in the study if a participant withdraws.

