### Randomization

There will be a total of 50 patients recruited, with 25 patients randomized to the intensive arm and 25 patients to the standard care arm. Randomization will be performed by a statistician using computer-generated random number sequence with an allocation ratio of 1:1 for each group.

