### Allocation

Computer generated codes numbered 1–50 will be used to assign patients to either the intensive arm or the standard care arm. The randomization procedures are as follows:
The physician or nurse will explain to eligible patients about the international recommendation on performing regular follow-up to detect silent risk factors and complicationsThey will also explain to patients the need to assess the effectiveness of using a team to implement structured care by comparing the latter with usual careAfter the patient has signed the consent form, a study team member will open the envelope containing the randomization group and sign and date the envelopeThe signed envelope will be kept by the nurse in a secure place for audit purposesThe nurse will explain to the patient whether they have been randomized to the intensive arm or standard care arm and the assessment will proceed accordinglyThe nurse will keep a log of randomized patients and record status including study completion, premature discontinuation, withdrawal of consent or loss to follow-up

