### Sample size

The proposed sample size of 25 participants in each group is adequate to estimate the mean of the eGFR between the two groups of participants, effect size (2.5-unit difference) using the *t* test (two-tailed alpha = 0.05 with statistical power of 0.80).

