### Statistical methods

Categorical data will be presented as frequency (percentage). Numerical data will be presented as mean (standard deviation (SD)), unless specified otherwise. Differences in baseline characteristics between two groups will be examined using the chi-square test or Fisher’s exact test for categorical variables and the two-sample *t* test or Mann-Whitney U test for continuous variables.

Logistic regression of binary outcomes such as cardiovascular events will be performed to determine the association between treatment group and potential risk factors and the outcomes. Relative risk (RR) (with 95% CI) will be calculatec. For continuous outcomes such as change in the MARS-5 and DDS17, linear regression will be used. Measure of tolerance for multicollinearity will be assessed. Coefficient B (with 95% CI) will be reported. The number of occurrences of hypoglycemia will be analyzed by Poisson regression. Measure of deviance will be checked and relative risk (RR) (with 95% CI) will be calculated.

*P* values < 0.05 will be deemed statistically significant. Statistical analysis will be performed using SPSS statistical software, version 19.0 (IBM Corp. Armonk, NY, USA). This RCT will be analyzed by the principle of intention to treat (ITT) and the per protocol (PP) approach.

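### The 80% power is stated for 25 patients per arm, exactly the number randomised, with no stated margin for loss over 3 years and no replacement

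*Protocol article*

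**What the plan says.** The Sample size section reads: "The proposed sample size of 25 participants in each group is adequate to estimate the mean of the eGFR between the two groups". It gives a 2.5-unit difference, a t test, and "two-tailed alpha = 0.05 with statistical power of 0.80". It states no SD, no time point for the eGFR comparison and no allowance for loss.

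The Randomization section fixes the same number as the number entered: "There will be a total of 50 patients recruited, with 25 patients randomized to the intensive arm and 25 patients to the standard care arm". The Allocation section has codes 1 to 50 only.

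Three other places bear on how many patients will supply an outcome:

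- The Eligibility criteria section lists three grounds for withdrawal (consent withdrawn; unable to continue or stopped on medical grounds; pregnancy) and then says "There will be no participant replacement in the study if a participant withdraws".
- The Allocation section has the nurse keep a log and "record status including study completion, premature discontinuation, withdrawal of consent or loss to follow-up".
- The Abstract gives the duration: "Follow up (FU) will be for 3 years".

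The Statistical methods section says: "This RCT will be analyzed by the principle of intention to treat (ITT) and the per protocol (PP) approach".

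**The concern.** A t test on eGFR uses only patients who have an outcome eGFR. The powered number and the randomised number are both 25 per arm. The article foresees patients leaving and rules out making up the number. Taken together, these statements tie the 80% to complete outcome data in all 50 patients for 3 years.

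The population makes that a demanding condition. The Abstract describes such patients as being at the highest risk of cardiovascular complications and renal failure, and related death is part of a primary endpoint.

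What is at stake is interpretation. Decline of eGFR belongs to the first primary endpoint, and eGFR is the only outcome with a power statement. If the renal comparison shows no difference, readers will judge it against 80% power, although the analysed numbers may have given less.

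**Working it through.** **Inputs from the article.** 25 per arm; difference 2.5 units; two-sided alpha 0.05; power 0.80; two-sample t test.

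**Inputs not in the article.** The SD of the eGFR measure and the loss rate. The SD is back-solved below. The loss rates are assumptions, shown as a range.

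**Step 1: the plan's own figure.** It cannot be reproduced, because no SD is given. It can only be inverted. With n per arm, standardised difference d = 2.5/SD, degrees of freedom 2n − 2 and noncentrality d × √(n/2), power is the probability that a noncentral t variable exceeds the two-sided 5% critical value. The opposite tail is negligible.

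- At n = 25 there are 48 degrees of freedom and the critical value is 2.011.
- Power of 0.80 needs noncentrality 2.859, so d = 2.859/√12.5 = 0.809.
- The implied SD is 2.5/0.809 = 3.09 units. The normal approximation gives 3.15.

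**Step 2: can the figure be read another way?**

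- If 2.5 were a standardised effect (SD = 1), 4 per arm would already give 84% power by t test and 25 per arm practically 100%. That does not lead to 25 at 80%.
- If the 25 contained a 20% allowance, so that 20 evaluable per arm gave 80%, the SD would be 2.75 and power at 25 would be 88%. The article attaches 0.80, not 0.88, to 25.

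The reading that fits the stated numbers is therefore 25 analysed per arm.

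**Step 3: power with fewer evaluable patients**, holding d at 0.809 and treating a lost patient as contributing nothing. The last column is the difference detectable at 80% under the same SD.

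| Evaluable per arm | Assumed loss | Power | Detectable difference (units) |
|---|---|---|---|
| 25 | 0% | 80.0% | 2.50 |
| 24 | 4% | 78.3% | 2.55 |
| 23 | 8% | 76.5% | 2.61 |
| 22.5 (average) | 10% | 75.5% | 2.64 |
| 22 | 12% | 74.6% | 2.67 |
| 20 | 20% | 70.3% | 2.81 |
| 18 | 28% | 65.4% | 2.97 |

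Worked row for 20 per arm: noncentrality 0.809 × √10 = 2.557, 38 degrees of freedom, critical value 2.024, power 0.703. For 80% power at n = 20, d must be 0.909, and 0.909 × 3.09 = 2.81 units.

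**Step 4: how much depends on the missing SD.** With all 25 per arm measured, power for 2.5 units is 93% at SD 2.5, 82% at SD 3, 58% at SD 4, 41% at SD 5 and 14% at SD 10. At SD 2.5, 20 per arm would still give 87%.

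**The case against.** The strongest reply is that the SD was chosen so that 25 per arm gives exactly 80%, after which fewer patients must give less. That is true of any trial and shows no wrong sum here. The article calls 25 adequate; it does not call it the minimum. A condensed article may leave an attrition allowance to the full protocol. Withdrawal criteria and a status log are routine provisions and predict no particular loss. Declining to replace randomised patients is not a fault and sits well with an intention-to-treat analysis.

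Much of this stands. A reader might infer that the plan expects substantial loss, or that its power fails even on its own SD. The article supports neither: it states no SD and no expected rate, and it provides for loss without forecasting it. Nor can an allowance inside the 25 be ruled out from this article, although the stated 0.80 does not match one (Step 2).

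A further fair point is that eGFR is collected at week 0 and before every endocrinologist review, and the renal endpoint is framed as a rate of decline. A patient who leaves after a year or more could still contribute a slope, so treating every leaver as a complete loss overstates the shortfall. The relief is partial, because the power statement is for a simple t test. Intention to treat does not by itself supply missing eGFR values.

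What the reply does not remove is that the article chose to print a number, a power and a no-replacement rule, and that the first two fit together only with no loss of outcome data.

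**Conclusion.** The point holds in a limited form. The stated power belongs to the full randomised number, no margin for loss is stated, and replacement is excluded. The 80% therefore describes the design only if all 50 patients contribute an outcome eGFR.

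The size of the shortfall is conditional on the back-solved SD of about 3.09 units, on assumed loss rates, and on lost patients contributing nothing. On those terms it is small for one loss per arm (about 78%) and moderate at 10% to 20% loss (about 76% to 70%).

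It would go too far to conclude that the trial is underpowered by a known amount. The unstated SD and time point matter more than attrition, since power with no loss at all already depends heavily on the SD (Step 4). This is a correction to a stated design property that is worth making. It does not call for a larger trial.

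**What to change.** Keep 50 patients and the no-replacement rule. Restate the Sample size section as power for evaluable patients, and give three items that are now absent: the SD assumed, the eGFR measure and time point it refers to, and the loss rate assumed. A possible form, with the sponsor's own values in the brackets: *Of 25 patients randomised per arm, [n] are expected to have an outcome eGFR at [time point], assuming [x]% loss. With an SD of [s], this gives [p]% power for a 2.5-unit difference, or 80% power for a difference of [d] units (two-sample t test, two-sided alpha 0.05).*

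For illustration only, 20% loss with the back-solved SD would put 20, about 70% and about 2.8 units in those places. The sponsor should not print these figures unless its own SD and loss rate support them. If the analysis will use the repeated eGFR values, the power can be stated for that analysis, which may recover part of the difference.

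The cost is a sentence or two and no extra patients. The downside is that the stated power becomes slightly less favourable.

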### Randomization

There will be a total of 50 patients recruited, with 25 patients randomized to the intensive arm and 25 patients to the standard care arm. Randomization will be performed by a statistician using computer-generated random number sequence with an allocation ratio of 1:1 for each group.

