## Introduction

### Background

The number of individuals with type 2 diabetes mellitus (T2DM) in Singapore, a Southeast Asian city-state with a population of 6.5 million, is estimated to grow from 400,000 to 670,000 by 2030 and to an alarming 1.0 million by 2050 with the continuing rise in the prevalence of obesity [1]. Total economic costs per working-age patient with T2DM in 2010 were estimated to be US$5,646, with total economic costs of US$787 million; this is estimated to rise to US$7,791 per patient and total economic costs of US$1,867 million by 2050 [2]. The presence of complications and need for inpatient care are major contributors to these increasing costs. Diabetic nephropathy is a major cause of morbidity and mortality. Asian ethnicity, uncontrolled hypertension and proteinuria are major risk factors for progression to end-stage renal failure [3]. Control of multiple risk factors, as in the Steno-2 study [4], has been shown to improve cardiovascular outcomes, increase the length of time free from incident cardiovascular disease, reduce the risk of death from all causes and reduce the progression of nephropathy as measured by worsening proteinuria, glomerular filtration rate (GFR) and serum creatinine. Previous trials have also suggested the utility of the chronic care model [5], structured recall [6], regular nurse contact [7], technology-enabled diabetes self-management education and support [8, 9] and a multifaceted approach in dealing with diabetes mellitus [6]. While most researchers have agreed that good glycemic outcomes are achievable through committing to appropriate intensive therapy and a team approach [10], there are multiple barriers to the implementation of quality diabetes mellitus care. In particular, barriers to good diabetes mellitus care can include the absence of a system to prioritize clinical resources for patients who require more intensive management, inadequate self-empowerment of patients, inadequate use of effective behavioral modification techniques, ineffective use of technology to enable diabetes self-management education and support and the need to self-fund glucose monitoring devices and monitoring and treatment consumables.

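### The renal comparison as described makes no use of week-0 urine albumin:creatinine ratio (ACR), although proteinuria is named as a major renal risk factor and patients enter with and without it

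*Protocol article*

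**What the plan says.** All of this is in the protocol article.

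- **Background:** "Asian ethnicity, uncontrolled hypertension and proteinuria are major risk factors for progression to end-stage renal failure". No ranking or effect size is given.
- **Eligibility criteria:** nephropathy means eGFR 30–60 ml/min "and/or proteinuria classified as urine protein" above 0.5 g/day, and/or ACR above 30 mg/mmol. A patient can therefore enter on eGFR alone, on proteinuria alone, or on both. The expected mix is not stated.
- **Randomization and Allocation:** the statistician allocates "using computer-generated random number sequence with an allocation ratio of 1:1 for each group", 25 to each arm. "Computer generated codes numbered 1–50 will be used to assign patients to either the intensive arm or the standard care arm". Neither section names a stratum.
- **Primary endpoints:** the first concerns the rate of deterioration of kidney disease, through eGFR decline or worsening proteinuria, or end-stage disease.
- **Sample size:** 25 per group is called "adequate to estimate the mean of the eGFR between the two groups of participants", for a 2.5-unit difference by t test ("two-tailed alpha = 0.05 with statistical power of 0.80"). No SD is given.
- **Data collection methods:** ACR and eGFR are both obtained at week 0.
- **Statistical methods:** logistic regression with treatment group and unnamed risk factors covers binary outcomes. Linear regression covers continuous outcomes, with MARS-5 and DDS17 as the examples. A collinearity check is planned. Neither eGFR nor a renal covariate is mentioned.

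**The concern.** The protocol identifies a renal prognostic factor, enrols across it and measures it at baseline. It then describes a renal comparison that does not use it at randomization or in the one test attached to eGFR. With 25 patients per arm, the two arms can easily end up with different proportions of proteinuric patients. An unadjusted difference in eGFR would then carry part of that imbalance. Even with a balanced split, leaving out a predictive baseline value gives up precision that the trial has already paid to collect. ACR is also the baseline of one component of the primary endpoint itself. Adjusting for baseline eGFR alone would not replace it, because the eGFR level does not tell who has proteinuria.

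**Working it through.** **1. The plan's own figure.** Inputs from Sample size: 25 per arm, difference 2.5, two-sided alpha 0.05, power 0.80. The SD is missing, so 25 cannot be reproduced directly. Solving for the SD that makes these inputs agree gives 3.09 with the t test. The normal approximation gives 2.5 / [(1.96 + 0.84) × √(2/25)] ≈ 3.15. I use 3.09. The standard error of the difference is then 3.09 × √(2/25) = 0.874.

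**2. Chance imbalance.** With arms fixed at 25:25 and K of 50 patients proteinuric, the number in one arm is hypergeometric (50, K, 25). K is not in the document; 40-60% is assumed.

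| K of 50 | Gap of at least 4 patients | Gap of at least 5 patients |
|---|---|---|
| 20 or 30 | 39% | 15% |
| 25 | 26% | 26% |

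The gap is always even when K is even and odd when K is odd. So the 15% refers to gaps of 6 or more (24 points). The 26% refers to gaps of 5 or more (20 points). These chances are two-sided; about half falls in each direction.

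**3. Size of the shift.** Let p be the proteinuric fraction and r the correlation between proteinuria and the eGFR outcome (assumed 0.3-0.5). The mean gap between patients with and without proteinuria is D = r × SD / √(p(1−p)).

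- p = 0.5, r = 0.3: D = 0.3 × 3.09 / 0.5 = 1.85
- p = 0.4 or 0.6, r = 0.5: D = 0.5 × 3.09 / 0.49 = 3.15

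The shift in the unadjusted difference is imbalance × D. At 24 points it is 0.24 × 1.85 = 0.44 up to 0.24 × 3.15 = 0.76. Divided by 2.5, that is 18% to 30% of the target. Divided by 0.874, it is about 0.5 to 0.9 standard errors.

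**4. What that does to the test, given the split.** Take D = 3, a 50/50 mix and a 20-point imbalance, so the shift is 0.20 × 3 = 0.6. The unadjusted test then has a conditional type I error of 7.4%. Conditional power is 60% if the split is adverse and 97% if it is favourable.

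**5. What it does on average.** Over repeated randomizations (40,000 simulated trials each at D = 3 and D = 6), the unadjusted t test rejects a true null in 4.9% and 5.1% of trials.

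**6. Gain from adjusting.** A covariate with correlation r multiplies the residual variance by 1 − r². The equivalent gain in patients is 1/(1 − r²): 1/0.91 = 1.10 at r = 0.3 and 1/0.75 = 1.33 at r = 0.5. With baseline eGFR also in the model, r should be read as the correlation that remains after baseline eGFR is accounted for.

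**The case against.** **Unstratified randomization is valid.** Chance imbalance is already part of the standard error, and step 5 confirms that overall type I error is kept. This stands in full. Stratifying a 50-patient pilot is a choice, not an obligation.

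**The analysis may already allow for proteinuria.** A t test used for sizing need not be the analysis model. The Statistical methods section plans regression, and a collinearity check implies several predictors. A covariate list could sit in an analysis plan or full protocol that is not shown. This stands in part: the document is silent on the point and does not exclude ACR. But its risk-factor wording is attached to binary outcomes, its examples of linear regression are questionnaire scores, and the only method it attaches to eGFR takes no covariate.

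**A reader might infer that a chance split could imitate or cancel the whole 2.5-unit effect.** The documents do not support that. Suppose proteinuric patients lost 2-4 mL/min/year more, a gap of 6-12 units over 3 years. A 24-point split would then move the estimate by 0.24 × 6 = 1.4 to 0.24 × 12 = 2.9 units. But an SD of 3.09 with a 50/50 mix caps the gap at 2 × 3.09 = 6.2 units, even if proteinuria explained all the variation. The true SD may well be larger, since a uniform spread of eGFR over 30–60 alone has SD 30/√12 = 8.7. Power for 2.5 units would then be only 17%, and the missing SD would be the more basic problem.

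**A reader might also take proteinuria to be the strongest predictor.** The Background section lists it as one of three major risk factors, without ranking them, and for progression to end-stage renal failure.

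**Conclusion.** The point holds as a matter of efficiency and of conditional bias, not of validity. As described, the renal comparison makes no use of week-0 ACR at allocation or in the test tied to eGFR. A gap of 5 or more proteinuric patients between arms has a 15-26% chance. A 24-point imbalance would shift the eGFR difference by about 0.4-0.8 units, or 18-30% of the target. That is enough to change power noticeably for the split obtained, but not enough to produce or erase the target effect alone.

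These figures rest on three things that the document does not state: a proteinuric share of 40-60%, a correlation of 0.3-0.5, and an SD of 3.09 solved from the sample-size statement. If the SD is larger, the shift in eGFR units grows in proportion, but its size relative to the standard error does not change. The change is worth making because it costs almost nothing.

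**What to change.** For the renal primary outcome, replace the plain t test with a linear model (ANCOVA) containing treatment group, week-0 log(ACR) and baseline eGFR, and state this before analysis. The cost is one sentence and one degree of freedom per covariate; both values are already collected. At r = 0.3-0.5 the gain from log(ACR) corresponds to about 10-33% more patients, which matters in a trial that does not replace withdrawals.

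If allocation has not started, an optional addition is two computer-generated envelope lists, for proteinuria present or absent at entry, each in permuted blocks, with that stratum in the model. The cost is a second envelope series and arms that may differ slightly from 25:25. The stratum and log(ACR) overlap, so the planned collinearity check should cover them. If envelopes are already in use, keep them and change only the model.
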